### Dietary intake

To assess subjects’ dietary intake, two 24-h food recalls will be completed at baseline and the end of the study. One of the 24-h recalls will be filled for one of the working days of the week and another in the weekend. Pictures of food commonly consumed in Iran, together with a set of common household measurement tools (glass, cup, soup bowls, plates, teaspoon, and tablespoon), will be provided to assist subjects in estimating the portion sizes of the food.

The food items will be analyzed for their energy and nutrient content using the Nutritionist IV software version 4.1 (First Databank Division, the Hearst Corporation, and San Bruno, CA, USA), modified for Iranian foods. An Iranian food composition table will be used as an alternative for foods like Iranian bread (four items), cheese (two items), Kashk (whey), fruits (two items), sweets (nine items), and industrial fruit juice (one item) not included in the United States Department of Agriculture (USDA) food composition table [31].

### Sunlight exposure

A sunlight exposure questionnaire will be used to assess sunlight exposure. This questionnaire includes three questions covering the history of sunlight exposure, such as duration of outdoor activity in minutes per day, as well as sunlight avoidance history, such as use of an umbrella and sun block lotion. Subjects are also asked about their clothing style, such as wearing long sleeves and hijab or veil. The validity and reliability of the questionnaire have been reported in a previous study in Iran [32].

### Physical activity levels

The short form of the International Physical Activity Questionnaire (IPAQ) will be applied to assess the physical activity level of participants (http://www.ipaq.ki.se 2017). IPAQ is a seven-point questionnaire measuring the level of activity. In this questionnaire, the first and second questions are related to the number of days and intensity of physical activity, the third and fourth questions are related to the number of days and the average physical activity, the fifth and sixth questions are related to the number of days and light physical activity, and finally, the seventh question is related to the amount of time spent sitting in the last 7 days. The reliability and validity assessment of IPAQ across 12 countries showed that it can be used in many settings and in different languages [33].

### Blood sampling

Venous blood samples will be taken by the registered staff nurses between 9 and 10 am. The blood samples will be allowed to clot for about 60 min and will be centrifuged for 10 min at 2000 G within 2 h. All the blood serum will be stored at − 25 °C for further analysis. Blood serum will be used for analyzing calcium, phosphorus, PTH, and 25(OH)D3 levels, at baseline and the end of the study. Calcium and phosphorus levels will be measured by colorimetric enzymatic test (Pars Azmoon) and enzymatic photometric UV test BILT1500, respectively. For hormonal testing such as PTH, which need more precise testing, the Electrochemiluminescence (ECL) procedure, by Cobas e411 for Hitachi/Roche company, Germany, will be used. 25(OH)D3 will be measured by enzyme-linked immune sorbent assay (ELISA; Monobind Inc., Lake Forest, CA, USA).

### Statistical analysis

Missing data will be imputed using the regression imputation method. Quantitative variables will be reported as mean (standard deviation) and qualitative variables will be reported as percentages. ANOVA and Chi-square tests will be used to compare quantitative and qualitative variables in the three groups. To evaluate the effect of vitamin D supplementation on visceral fat mass, visceral fat percentage, lean mass, body fat percentage, waist circumference, FMI, RFM, BMI, and biochemical factors such as serum 25(OH)D, PTH, calcium and phosphorus levels two-way Repeated Measures ANOVA (RMA) will be applied in SPSS software version 21 (SPSS Inc., Chicago, USA). RMA assesses whether the mean changes in the results from baseline to 12 weeks differ in the three groups. This statistical analysis measures time to group interaction term. There are no planned interim analyses. The 95% confidence level will be considered.

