### Sample size estimation

Sample size was calculated according to Roosta et al. [29] using two mean comparison formula. In this formula, considering α = 0.05, β = 0.2, and mean (standard deviation) of waist circumference changes after supplementation with vitamin D, which was equal to 1.91 cm (1.7) and 0.55 cm (1.04), respectively, in the intervention and control groups, sample size is estimated as 18 subjects. Since, there are three groups in this study, the calculated sample size was multiplied with $$ \sqrt{number\ of\ groups} $$, and finally the desired sample size for this study was obtained as 90 subjects (30 subjects per group).

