### Strengths and limitations of the study

The strengths of our protocol study include assessing the different doses of vitamin D supplementation to treat vitamin D deficiency in nursing women with BMI of 25 kg/m^2^ and higher.Also, this study is the first study evaluating the effects of different amounts of vitamin D supplementation on anthropometric status and body composition in nursing women with BMI of 25 kg/m^2^ and higher.Body composition measurements are not assessed by gold standard techniques, which can be considered as a limitation of this study.Possible poor cooperation of some patients is another limitation of this study.The calculated sample size is another limitation of this study. Due to financial constraints, the number of subjects is limited to 90. As such, a 10% dropout is considered the maximum.

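### Regression imputation, read as one filled-in value per gap, carries no imputation uncertainty: at 10% dropout it either inflates the 5% tests to about 7–9% or dilutes the effect by about 10%

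*Protocol article*

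**What the plan says.** The Statistical analysis section has one rule for missing data: "Missing data will be imputed using the regression imputation method". It names no predictors, no random residual, no number of imputations and no pooling step.

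The outcomes are then compared by two-way repeated measures ANOVA through the time-by-group term; the section explains that "RMA assesses whether the mean changes in the results from baseline to 12 weeks differ in the three groups". On the test level it says "The 95% confidence level will be considered".

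Table 1 gives two measurement times, months 0 and 3. Sample size estimation sets 30 women per group, 90 in total. On attrition, Strengths and limitations says "As such, a 10% dropout is considered the maximum".

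**The concern.** A value predicted by regression adds no information about the woman who left, but an ordinary ANOVA counts it as a full observation. What follows depends on whether treatment arm is among the predictors.

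- **Arm in the imputation model.** Imputed values lie on their own arm's fitted line. They add degrees of freedom and no residual scatter, so the error variance is understated and the tests reject too often.
- **Arm left out.** Imputed women in all three groups are placed on one common line. The groups are drawn together and the treatment effect is diluted.

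The rule covers all missing data, so it feeds every outcome listed for RMA. The Discussion says the results are meant to identify the best dose and may be used to persuade governmental organisations to provide supplements, so both false positives and diluted effects matter.

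**Working it through.** **Inputs from the protocol article.** 30 per group and three groups (Sample size estimation); test level 5% (Statistical analysis); dropout at most 10% (Strengths and limitations), so 27 observed and 3 imputed per group if spread evenly; two visits (Table 1).

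**Assumptions, not in the document.** One imputed value per gap; baseline complete and used as predictor; week-12 values missing completely at random; baseline to week-12 correlation ρ of 0.5, 0.8 or 0.95; unit SD at each visit.

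**Step 1. The plan's own figure.** For waist change of 1.91 (SD 1.7) against 0.55 (SD 1.04) cm, the difference is 1.36 and the pooled variance is (1.7² + 1.04²)/2 = 1.986. With two-sided α = 0.05 and power 80%, n = 2 × (1.960 + 0.842)² × 1.986 / 1.36² = 16.9 per group, or 17.9 by a t-based calculation. This agrees with the plan's "sample size is estimated as 18 subjects". Multiplying by √3 gives 17 × 1.732 = 29.4 or 18 × 1.732 = 31.2, in line with the stated 30 per group. The sample size is not in dispute here.

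**Step 2. Which test is affected.** With two visits, the RMA time-by-group test is the same as a one-way ANOVA on change from baseline.

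**Step 3. Standard error with arm in the model, ρ = 0.8.** Write week 12 = ρ × baseline + residual. The variance of change splits into a baseline part, (1 − ρ)² = 0.04, and a residual part, 1 − ρ² = 0.36.

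- True SD of a pairwise difference: all 30 baselines contribute, but only 27 residuals. √[2 × (0.04/30 + 0.36/27)] = √0.02933 = 0.171.
- SE that ANOVA reports: the 27 observed residuals carry about 26 degrees of freedom per arm, but the sum of squares is divided by 29. √[2 × (0.04 + 0.36 × 26/29)/30] = √0.02418 = 0.156.
- Ratio 0.156/0.171 ≈ 0.91, so the SE is about 9% too small. The 1.96 cut-off then acts like 1.96 × 0.908 = 1.78, a two-sided error of about 7.5%.

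**Step 4. Simulation** (40,000 trials per setting, 3 × 30, arm in the model, no random residual, 10% missing):

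| ρ | Reported SE | True SD | Ratio | Pairwise type I | Three-group F type I |
|---|---|---|---|---|---|
| 0.5 | 0.247 | 0.270 | 0.915 | 7.2% | 7.9% |
| 0.8 | 0.155 | 0.171 | 0.906 | 7.5% | 8.4% |
| 0.95 | 0.077 | 0.086 | 0.895 | 7.7% | 8.8% |

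At 5% missing, the F test runs at 6.1–6.6% and the pairwise test at 5.7–6.2%. Adding one random residual to each prediction does not repair it: at 10% missing, F is 7.7–8.4% and pairwise 6.9–7.4%.

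**Step 5. Arm left out, 10% missing.** Imputed women contribute on average no difference between arms, so the expected estimate is 0.9 × Δ + 0.1 × 0 = 0.9Δ. Simulation agrees: a true difference of 1.00 is estimated as 0.90, with type I error 4.9–5.0%. On the planning difference, 1.36 cm would be estimated as about 0.9 × 1.36 = 1.22 cm.

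**Step 6. Observed cases only, 10% missing.** The F test runs at 5.0% and the pairwise test at 4.7–5.1%. Reported and true SE agree (0.172 and 0.172 at ρ = 0.8).

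**Step 7. Multiple imputation.** With 20 sets, arm and baseline in the model, Rubin's rules, ρ = 0.8 and 2,000 trials, the pairwise test runs at 4.9%.

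**The case against.** **The text does not say single.** The article says only regression imputation, and a condensed article commonly leaves predictors and similar detail to a fuller document. This stands in part: single imputation is a reading, and whether arm is a predictor is unknown. But the article names a method and follows it with ordinary ANOVA. A fuller plan could make that valid only by changing or substantially qualifying the sentence, so this is more than a missing detail.

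**The two harms exclude each other.** This stands. A reader might infer that every p-value and interval in the trial would be wrong, or that the tests run at 7–8% whatever happens. The document supports neither. Inflation needs arm in the model; without it, false positives are controlled and the cost is a conservative dilution.

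**10% is the protocol's maximum.** This also stands. At 5% missing the inflation is small, and with no missing data there is none. Scenarios beyond 10% lie outside the plan's own figures.

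**Imputation can recover real information.** If only one measure is missing and correlated week-12 measures exist, such as weight or fat mass, the harm is smaller. With an auxiliary of assumed partial correlation 0.8, the F test at 10% missing fell from 8.1% to 5.9%. This does not help women who drop out entirely, which is what the 10% figure describes.

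**Replacing RMA by baseline-adjusted ANCOVA goes beyond the defect.** Agreed. A reader might infer that the imputation flaw condemns RMA, but the planned comparison of change holds its level on observed data.

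**Conclusion.** The concern holds in a conditional form. The stated method, on its natural reading, carries no imputation uncertainty into the tests. At the protocol's 10% maximum dropout:

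- **With arm in the imputation model,** SEs are about 9–11% too small and the nominal 5% tests run at about 7–9%.
- **With arm omitted,** the level is kept and the effect is diluted by about 10%.

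These figures rest on data missing completely at random, on baseline as the only predictor and on assumed correlations, across which the results vary little. The document does not show which branch applies.

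The error is moderate, confined to the analysis and easily corrected. It should be fixed before analysis, but it does not affect the conduct of the trial or its sample size.

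**What to change.** Replace the sentence on regression imputation with wording to this effect: the primary analysis uses all observed week-12 values without single imputation, by the planned group comparison of change or by a likelihood mixed model. As a sensitivity analysis, missing values are multiply imputed (at least 20 sets; arm, baseline value and the age and BMI stratification factors in the model) and results are combined by Rubin's rules.

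Baseline-adjusted ANCOVA is an optional, separate improvement that this point does not require.

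**Cost.** Analysis wording only, with no new data or participants. Intervals become slightly wider: at 10% missing and ρ = 0.8 the SE is 0.172 instead of the understated 0.155, about 11% more (0.172/0.155 = 1.11). Power for a single pairwise comparison at the planning difference of 1.36 cm is about 94% with 27 observed per group, against 96% with 30, so the 80% target is still met.

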**Fig. 1 Fig1:**
[figure not shown]
Recruitment flow chart

Four types of questionnaires will be completed by each subject at the beginning and end of the study: socio demographic, 24-h recalls to collect dietary intake data, sunlight exposure questionnaire, and physical activity questionnaire (International Physical Activity Questionnaires (IPAQ)).

The necessary information on anthropometric measurements (height, weight, BMI, body fat percentage, body weight (kg), lean mass (kg), visceral fat, and visceral fat mass (kg), relative fat mass index (RFM), fat mass index (FMI) will be obtained using In Body model 270 as a body composition analyzer (In Body Co., Ltd, Seoul, Korea). Serum levels of vitamin D, PTH, as well as calcium and phosphorus levels will be measured at the beginning and end of intervention. Table 1 shows the primary and secondary outcome measures and the time for measurement and a Standard Protocol Items: Recommendations for Interventional Trials (SPIRIT) checklist is included as Additional file 1. The anthropometric and body composition measures, including height, weight, BMI, body fat percentage, body weight, lean mass, visceral fat and visceral fat mass, RFM, and FMI were intended to be primary outcomes but were unintentionally omitted in the preregistration. However, our sample size calculation is based on waist circumference as intended as a primary measure.

**Table 1 Tab1:** Outcome measures and measurement times

	Months	
	0	3
Primary outcomes		
Blood analysis		
Serum 25(OH)D	*	*
Serum PTH	*	*
Serum calcium	*	*
Serum phosphor	*	*
Anthropometry and clinical assessment		
Height (cm), weight (kg)	* *	*
Body mass index (kg/m^2^)	*	*
Waist circumference (cm)	*	*
Body composition		
Fat mass (kg)	*	*
Lean mass (kg)	*	*
Body fat (%)	*	*
Visceral fat mass (kg)	*	*
Fat mass index (FMI)	*	*
Relative fat mass index (RFM)	*	*
Secondary outcomes		
Weight (kg), height (cm), head circumference (cm), of the infants	*	*
Infection frequency in infants		*
Frequency of doctor visits		*

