### Inclusion and exclusion criteria

Inclusion criteria are as follows:
Nursing women with overweight (BMI 25–29.9 kg/m^2^) or obesity (BMI 30–39.9 kg/m^2^)Aged 20–49 years oldDelivered at term (gestational age of 37–42 weeks)Normal birth weight (2500–3900 kg)Declared exclusive nursing for the next 3 months

The exclusion criteria are:
PregnancyHaving gastrointestinal disorders interfering with bowel function, severe hepatic, renal (dialysis), inflammatory, cancer, diabetes, hypertension, epilepsy, and thyroid diseases, or taking any medicationRegular intake of vitamin D supplements or multivitamins (once or more per week)History of smoking or alcohol consumption once or more per week in the past monthAdhering to a specific diet during the past 3 months

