## Abbreviations

25(OH)D: 25-Hydroxy-vitamin D
ANOVA: One-way analysis of variance
BFP: Body fat mass percentage
BIA: Body impedance analyses
BMI: Body mass index
ECL: Electrochemiluminescence
ELISA: Enzyme-linked immunosorbent assay
FMI: Fat mass index
IOM: Institute of Medicine
IPAQ: International physical activity questionnaire
PTH: Parathyroid hormone
RFM: Relative fat mass
RMA: Repeated measures ANOVA

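### Infant weight, length and head circumference are measured at birth and at month 3, but no stated analysis adjusts for the birth value; doing so is a nearly free gain in precision

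*Protocol article*

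**What the plan says.** In the protocol article, Table 1 (Study design) gives as a secondary outcome "Weight (kg), height (cm), head circumference (cm), of the infants", marked at month 0 and month 3.

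The Statistical analysis section states two methods for quantitative variables. The first is general and names no outcome, time point or covariate: "ANOVA and Chi-square tests will be used to compare quantitative and qualitative variables in the three groups". The Abbreviations give "ANOVA: One-way analysis of variance". The second is two-way repeated-measures ANOVA, introduced by a list that begins "To evaluate the effect of vitamin D supplementation on visceral fat mass, visceral fat percentage, lean mass, body fat percentage, waist circumference" and ends with maternal biochemistry. No infant variable is on it. The same section says that this method tests whether mean changes over 12 weeks differ between the three groups. No baseline covariate is mentioned for any outcome.

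**The concern.** If the infant measures follow the only general rule stated, their group comparison is a one-way ANOVA. Run on month-3 values, it leaves the month-0 value unused. Run on changes, it forces that value to enter with a coefficient of 1, whatever the data show. Repeated-measures ANOVA with two time points is equivalent to an ANOVA of change, so moving the infants to that list would not solve the problem.

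All of these analyses are unbiased under randomisation. What is at stake is precision in three secondary outcomes. The limitations section says finances hold the trial to 90 women, so precision cannot be bought by recruiting more. The month-0 values are already scheduled.

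**Working it through.** **Inputs from the article.** Three arms of 30 (Sample size estimation), allocated 1:1:1. For losses, the limitations section says "As such, a 10% dropout is considered the maximum", so n = 27 per arm and N = 81 at the worst. The trial's sample size rests on maternal waist circumference and has no bearing here, and the article gives no planning figure for infant outcomes to reproduce.

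**Inputs assumed.** The article gives neither r, the correlation between month-0 and month-3 values, nor k, the ratio of the month-0 SD to the month-3 SD. Both are shown over a range.

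**Formulas.** 95% interval half-width for one dose minus placebo, in SDs of the month-3 value:

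- Raw month-3: t(0.975, N−3) × √(2/n)
- Change score: t(0.975, N−3) × √[(2/n)(1 + k² − 2kr)]
- Adjusted for month 0: t(0.975, N−4) × √[(2/n)(1 − r²)(1 + 1/(N−5))]

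The last factor in the adjusted formula is the expected cost of chance baseline imbalance.

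**Raw against adjusted, n = 27.** Raw: 1.991 × √(2/27) = 1.991 × 0.272 = 0.542. Adjusted at r = 0.5: 1.991 × √(0.0741 × 0.75 × 1.0132) = 0.472.

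| r | Adjusted | Change against raw (0.542) |
|---|---|---|
| 0.1 | 0.543 | 0.2% wider |
| 0.2 | 0.534 | 1.4% narrower |
| 0.3 | 0.520 | 4.0% narrower |
| 0.5 | 0.472 | 12.8% narrower |
| 0.6 | 0.436 | 19.5% narrower |

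Break-even is at r = 0.116. With all 30 per arm, the raw half-width is 0.513 and the adjusted values are 0.514, 0.506, 0.493, 0.447 and 0.413; the percentages barely move.

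**Change score against adjusted, n = 27.** Each cell gives the change-score half-width, then how much narrower the adjusted interval is.

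| r | k = 1.0 | k = 0.8 | k = 0.6 |
|---|---|---|---|
| 0.3 | 0.641; 19% | 0.584; 11% | 0.542; 4% |
| 0.5 | 0.542; 13% | 0.497; 5% | 0.472; 0% |
| 0.6 | 0.485; 10% | 0.447; 2% | 0.433; −0.7% |

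**Largest possible loss.** Adjusting does worst at r = 0 against raw values and at r = k against change scores. In both cases the ratio is t(0.975, 77)/t(0.975, 78) × √(1 + 1/76) = 1.007, so the expected interval is about 0.7% wider.

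**Simulation check.** In 4000 simulated trials with n = 27, mean half-widths were within about 0.005 SD of the formulas (for example 0.540 raw and 0.471 adjusted at r = 0.5). Coverage was 0.945 to 0.954 for every method.

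**Restricted birth weight.** The inclusion criteria limit birth weight to 2500–3900 (printed as kg, read here as g), which lowers r for weight. Assume a normal distribution before selection with mean 3100–3400 g and SD 400–500 g. Truncation then shrinks the SD by a factor u = 0.69 to 0.82, and r′ = r·u/√[1 + r²(u² − 1)]. An unrestricted r of 0.3 becomes 0.21–0.25 (gain over raw 1.6–2.5%), 0.5 becomes 0.37–0.43 (6.6–9.0%), and 0.6 becomes 0.46–0.52 (10.7–14.2%).

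**The case against.** The strongest reply is that the article never says one-way ANOVA governs the infant outcomes. The ANOVA and chi-square sentence directly follows the descriptive statistics, and the next sentence turns to treatment effects with another method, so it may cover only descriptive or baseline comparisons. The repeated-measures list also omits maternal weight and fat mass in kg, both primary outcomes in Table 1, so it may simply be incomplete. If so, the infant model is unspecified, and a journal article may leave that to a fuller document.

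Much of this stands: the assignment to one-way ANOVA is an inference. It does not remove the point, because neither method the article names adjusts for baseline. If the infants belong on the repeated-measures list, the change-score table applies instead.

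Other objections stand in part:

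- The gain depends on r and k, which are unknown, and it may be nil. The birth-weight limits also tend to lower k for weight, so the k = 1 column is generous for that outcome.
- The plan imputes missing data by regression, whereas the widths above use 27 complete cases per arm. The results for 30 per arm show that the percentage gains hardly change.
- All three stated objectives are maternal, and unadjusted analysis is valid. This limits the weight of the point, not its direction.
- Asking for dose-minus-placebo estimates with intervals is a reporting matter separate from adjustment. It is included because the intervals are wide enough for a non-significant result to be misread.

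**Conclusion.** The point holds as an optional improvement. The infant measures are scheduled twice, are absent from the repeated-measures list, and have no baseline covariate under either stated method.

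The gain is small to modest. Against raw month-3 values it runs from nothing at r near 0.1 to about 20% narrower at r = 0.6, with weight towards the lower end because of the birth-weight limits. Against change scores it runs from 19% narrower to 0.7% wider over the r and k examined. The conclusion rests on assumed correlations and SD ratios and on an inferred reading of the ANOVA sentence, so confidence is medium.

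There is no bias, and type I error, the sample size and the primary conclusions are unchanged. Under any of these models the infant intervals remain wide, about 0.4 to 0.5 SD either side with adjustment. A non-significant infant result should therefore be read from its interval and not taken as evidence of no effect.

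**What to change.** Add to the Statistical analysis section:

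> Infant weight, length and head circumference at month 3 will each be compared between groups by analysis of covariance with the month-0 value of the same measure as the covariate. Each dose minus placebo will be reported with a 95% confidence interval.

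No other covariate is required. The cost is two sentences, three models and one degree of freedom in each. Both measurements are already scheduled, so there are no extra participants, visits, data or staff.

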## Methods/design

### Study design

Subjects will be randomly assigned into groups with a 1:1:1 randomization ratio. A flow chart of the study protocol is presented in Fig. 1.

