### Randomization

This study is a double-blind, randomized, placebo-controlled, parallel trial. Subjects will be randomly assigned to three treatment groups using computer-generated codes. Randomization will be conducted by an assistant using permuted block randomization method and stratified randomization will be used to match the subjects based on age (20–34 and 35–49 years old) and BMI (25–29.9 and 30–39.9 kg/m^2^). Subjects will be randomly allocated into three groups of 2000 IU vitamin D/d (VD1), 4000 IU vitamin D/d (VD2), and placebo (P), and will be followed up for 12 weeks.

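### The planned repeated measures ANOVA is valid but amounts to a change-score test without the randomisation strata; ANCOVA would be at least as efficient in large samples, though with almost no gain for waist circumference

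*Protocol article*

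**What the plan says.** The Statistical analysis section of the protocol article states that "two-way Repeated Measures ANOVA (RMA) will be applied in SPSS software version 21" for visceral fat, lean mass, body fat percentage, waist circumference, FMI, RFM, BMI and the four blood measures. It explains that the model compares the three groups on mean change over the 12 weeks through the interaction of time and group. Of the interval level it says only that "The 95% confidence level will be considered". Table 1 gives two measurement times for these outcomes, months 0 and 3.

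On allocation, the Study design section says "Subjects will be randomly assigned into groups with a 1:1:1 randomization ratio". The Randomization section adds that "stratified randomization will be used to match the subjects based on age" (20–34 and 35–49 years) and BMI (25–29.9 and 30–39.9 kg/m²), which makes four strata. The article names no baseline covariate, stratum term or other adjustment for the outcome analyses.

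**The concern.** With two time points, the time-by-group F test is algebraically the one-way ANOVA of change scores across arms. Subtracting the whole baseline value is the same as fixing the regression slope of week 12 on baseline at 1. If the true slope is lower, the change score over-corrects any chance difference in baseline and carries noise that a fitted slope would remove.

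The strata raise a second, smaller issue. Stratified allocation balances age group and BMI group across arms. If these factors predict change and the model leaves them out, the standard error does not reflect that balance, and the test tends to be conservative.

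What is at stake is precision, not validity. It matters here because the Strengths and limitations section says that funding caps the trial at 90 women and lists sample size as a limitation. The analysis is therefore one of the few places left to gain precision.

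**Working it through.** **Inputs from the article (Sample size estimation unless stated)**
- Error rates: "considering α = 0.05, β = 0.2". Sidedness is not stated; I take two-sided.
- Mean (SD) change in waist, intervention and control: "1.91 cm (1.7) and 0.55 cm (1.04". The difference is 1.91 − 0.55 = 1.36 cm. The root-mean-square SD of change is √[(1.7² + 1.04²)/2] = √1.986 = 1.41 cm.
- Maximum dropout is 10% (Strengths and limitations), so 27 per arm and 81 completers.
- Not given: the correlation r between baseline and week 12, and the between-woman SDs. Both are assumed ranges below.

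**1. The plan's own figure.** n per group = 2(1.960 + 0.842)² × 1.986 / 1.36² = 16.85, so 17; the t-based version gives 18. This agrees with "sample size is estimated as 18 subjects", read as per group. Multiplying by √3 gives 29.4 from 17 and 31.2 from 18, against "90 subjects (30 subjects per group". The planning inputs are therefore understood. At this effect, 27 per arm gives about 94% power for one pairwise comparison without multiplicity adjustment.

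**2. Variance of the two analyses.** With a common SD s at both times:
- Var(change) = 2s²(1 − r)
- Var(ANCOVA residual) = s²(1 − r²)
- Ratio = (1 + r)/2

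| r (assumed) | Ratio | Saving | 30 per arm is worth |
|---|---|---|---|
| 0.5 | 0.75 | 25% | 40.0 |
| 0.7 | 0.85 | 15% | 35.3 |
| 0.9 | 0.95 | 5% | 31.6 |
| 0.95 | 0.975 | 2.5% | 30.8 |

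If the week-12 SD is k times the baseline SD, the ratio is (1 − r²)k²/(1 + k² − 2rk). At r = 0.9 this is 0.61 for k = 0.8 and 0.98 for k = 1.2, so the equal-SD assumption matters.

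**3. What the planning figures imply for waist.** Setting 2s²(1 − r) = 1.986 gives r = 1 − 1.986/(2s²).
- s = 5 cm (assumed): r = 1 − 1.986/50 = 0.960, ratio 0.980, saving 2.0%.
- s = 10 cm (assumed): r = 1 − 1.986/200 = 0.990, ratio 0.995, saving 0.5%.
- Conversely, r = 0.5 would need s = √1.986 = 1.41 cm, and r = 0.9 would need √(1.986/0.2) = 3.15 cm. The first is not credible for women with BMI from 25 to 39.9.

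**4. Cost in degrees of freedom.** The change-score ANOVA on 81 women leaves 81 − 3 = 78. ANCOVA adds one term each for baseline, age stratum and BMI stratum, leaving 75. A rough small-sample allowance of 1 + 3/74 = 1.04 turns the ratio of 0.98 into 1.02, so for waist the gain and the cost roughly cancel. The allowance is pessimistic, because stratification already balances two of the three covariates.

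**5. Simulation.** Three arms of 27, permuted blocks within four strata, an effect in one arm, a 2-df F test and 4,000 runs; the stratum frequencies and the BMI–baseline link were assumed. ANCOVA includes baseline and both strata.

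| r | Power: change score | Power: ANCOVA | Type I: change score | Type I: ANCOVA |
|---|---|---|---|---|
| 0.5 | 82.2% | 91.2% | 3.8% | 4.8% |
| 0.7 | 81.8% | 87.0% | 3.9% | 4.9% |
| 0.9 | 81.8% | 83.0% | 4.7% | 4.8% |
| 0.95 | 82.2% | 82.3% | 5.0% | 5.2% |

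The Monte Carlo standard error is about 0.3 points near 5%, so the conservatism at r = 0.5 and 0.7 is real and the differences at r = 0.95 are noise. ANCOVA with baseline alone had power of 91.5%, 87.8%, 83.1% and 82.7%. The strata thus added nothing beyond baseline here, as expected when they act only through the baseline value.

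**The case against.** The strongest reply is that nothing here is an error. Under randomisation the expected baseline difference is zero, so the change-score comparison is unbiased. It also fits the sample size section, which plans on changes in waist. This stands. A reader might infer that regression to the mean or chance imbalance biases the planned estimate. The document does not support that: imbalance affects the precision of the estimate and how it reads in a given realisation, not its average over randomisations.

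Second, the gain is negligible for the sizing outcome, and power at the planned effect is already about 94%. This also stands, subject to the assumed waist SD, equal SDs and a planning SD taken from another study. A reader might quote the low-r rows as if they applied to the whole trial; the article's own SD of change rules that out for waist.

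Third, blood outcomes might be said to lose most. The article gives no correlation or SD for them, so this is an expectation and not a finding.

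Fourth, the strata may seem to be pure lost precision. Differencing already removes any stratum effect that is constant over time. Only an effect on change remains, and part of that acts through baseline.

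Finally, covariates could be left to an analysis plan that is not shown. This carries less weight, because the article names the model, the term tested and what it measures. It is a stated choice, not an omitted detail.

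**Conclusion.** The point holds as a low-cost gain in efficiency. The planned test is valid. It fixes the baseline slope at 1, leaves out the strata, and can be slightly conservative (simulated type I error 3.8% at r = 0.5, 5.0% at r = 0.95). In large samples ANCOVA is never less precise.

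The benefit differs by outcome. For waist circumference it is about 0.5 to 2% of variance, less than one woman per arm, and about nil once the extra degrees of freedom are counted. For outcomes with lower baseline correlation, plausibly 25(OH)D or PTH, it could reach 15 to 25% if r is 0.5 to 0.7. Those values of r are assumptions, and the percentages also assume equal SDs at both times. The document does not support the conclusions that the analysis is invalid, that the estimates are biased, or that this choice leaves the trial underpowered at its planned effect.

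**What to change.** Replace the repeated measures ANOVA in the Statistical analysis section with wording such as:

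> For each outcome, the week-12 value will be analysed by ANCOVA with treatment arm, the baseline value of the same outcome, age stratum and BMI stratum as terms. For BMI as outcome, continuous baseline BMI will stand in for the BMI stratum. The arm effect will be tested on two degrees of freedom, and adjusted differences between arms will be given with 95% confidence intervals.

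Settle this before unblinding, so that adjustment does not become a choice made after any baseline imbalance is seen. The cost is about 3 of about 78 residual degrees of freedom. No extra women, measurements or software are needed, and the sample size calculation can stay as it is.
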